### Sample size estimation

As this study had been designed as a cluster randomised trial, a sample size estimation was proposed which would highlight a significant difference between the two randomised groups in terms of the incidence of new cases of patients bringing up the topic of PE with their GP. It takes into account an intra-cluster correlation coefficient (ICC) varying between 0.05 and 0.20 and includes a recruitment of around 15 patients per GP [29]. In order to take into account between- and within-GP variability, expressed by intra-class correlation coefficient (ICC), this sample size must be increased by an inflation factor: 1 + (*m* − 1). ICC, with *m* the (mean) number of patients included by each GP. According to the literature [29, 30], it is not so easy to determine the appropriate value of ICC. It depends of many factors. We have chosen to fix ICC between 0.05 and 0.20, according to previous references. With 15 patients included by each GP, sample size estimation was 360 for ICC equals 0.05 and 800 for ICC at 0.20, and around 960 for ICC at 0.25. Furthermore, it is usual to observe a Hawthorne effect in this type of study. In our feasibility study, the incidence of patients who brought up PE with their GP in the CG was 6.6%. Following the guideline of PE updated by the ISSM, ‘5% of the population have an ejaculation latency of less than 2 minutes’ [8]. We estimated the incidence in the CG at around 5%. Usually in individual randomisation, *n* = 101 patients in total is necessary to highlight an absolute difference between 5 and 20%. For a two-sided type I error, *α* equals 0.05 and has a statistical power of 90%. Also, taking these aspects into account 600 patients, recruited by 40 GPs, must be included and then divided into 300 patients in each arm.

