**Methods:**

A cluster randomised controlled trial, stratified over four areas comparing an intervention group, which will receive the six strategies training session, and a control group, which ensures routine medical care. The primary outcome is to investigate the efficacy of a training in communication skills directed towards this pathology, compared with usual care procedures, on the incidence of patients bringing up the topic of PE with their GP. The secondary objective relates to the variation in the quality of life of patients after having recently addressed the topic of PE. Quality of life will be evaluated using the SF-12 health scale, with scoring filled in by the patient immediately after the consultation and 4 weeks later. The patients suffering from PE will be identified if their score is higher than 9 on the Premature Ejaculation Diagnostic Tool filled in 4 weeks after the consultation. The number of patients necessary to highlight a significant difference between the two groups from 5 to 20% is 101. Therefore, a total of 600 patients is expected, 300 in each arm (40 GPs, 15 patients per GP; risk *α* = 5%; power = 90%; intra-cluster correlation coefficient *ρ* = 0.2; Hawthorne effect = 15%; lost-to-follow-up rates for GPs = 10% and for patients = 20%).

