### Feasibility

As far as we are aware, this interventional multicentre study will be the first one concerned with PE in the area of primary health care. We created a pilot intervention study in primary care in order to estimate the feasibility of such a study design, as well as the incidence of diagnosed PE with, and without, the use of strategies. Thirteen GPs agreed to participate in the IG, six of whom included their patients in the study. Twenty-four GPs participated in the CG, 13 of whom included their patients in the study. The GPs in the IG included 26 of their patients in the study. They identified eight patients suffering from PE: 30.8%. The GPs in the CG included 61 of their patients. Among them, four were suffering from PE: 6.6% (*p* value = 0.004, OR = 6.6768, 95% confidence interval (CI) (1.55; 34.40)).

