#### Statistical methods

Analyses will be performed using Stata software, version 13 (StataCorp, College Station, TX, USA). All data will be analysed on intention to treat. The tests will be two-sided, with a type I error set at *α* = 0.05. Baseline characteristics (GPs and their patients) will be presented for each randomisation group as the mean ± standard deviation (SD) or the median (interquartile range) according to statistical distribution for continuous data and according to the number of patients and associated percentages for categorical parameters.

The comparisons between the randomised groups will be carried out using the Student *t* test or the Mann-Whitney test where appropriate, (1) normality verified by the Shapiro-Wilk test and (2) homoscedasticity by the Fisher-Snedecor test for quantitative parameters and using chi-squared or Fisher’s exact tests for categorical variables.

Outcomes will pertain to the cluster level using usual statistical tests and with more specific approaches at the individual level. Hierarchical regression models (generalised linear mixed model due to binary endpoint) will be performed as primary analysis: (1) to estimate the effect of intervention on the incidence of new cases of patients suffering from acquired and lifelong PE, natural variable PE and premature-like ejaculatory dysfunction and (2) to take into account the variability between and within, the GP cluster groups. Intra-class correlation coefficients will be presented by arm with a 95% CI. Then, GP characteristics (gender, age, geographical area) or patient characteristics (age, socioeconomic status) should be considered as covariate (fixed effects in mixed models) in adjusted multivariable analyses. The adjusted and unadjusted results will be presented: absolute numbers of patients who have raised the topic of PE with their related GP, relative risks and 95% CIs.

For secondary endpoints, comparisons at the individual level between randomised groups will be performed using an analysis of covariance for correlated data with the baseline score as a covariate, as suggested by Klar and Darlington [31] for the SF-12 quality of life scores. Results will be expressed as effect-sizes and 95% CIs. The PEDT will be analysed as a quantitative score using statistical methods described for the SF-12 quality of life and as a binary outcome (< ≥ 11) with the use of a generalised linear mixed model.

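### The 90% power claimed for 40 GPs and 600 patients is about 82% at the abstract's own ICC of 0.20, and it depends on a cluster size of 15 that the protocol does not reconcile with its pilot

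*Protocol article*

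**What the plan says.** The protocol article gives the design in two places. The Methods part of the abstract lists "40 GPs, 15 patients per GP", an ICC of 0.2, 90% power, a 15% Hawthorne effect, and losses of 10% of GPs and 20% of patients. The section Sample size estimation "includes a recruitment of around 15 patients per GP" and defines *m* in the inflation factor as a mean. It takes the ICC as a range from 0.05 to 0.20 and gives totals of 360, 800 and about 960 patients for ICC 0.05, 0.20 and 0.25. It says that 101 "patients in total is necessary to highlight an absolute difference between 5 and 20" per cent, states that the calculation "has a statistical power of 90" per cent, and concludes that "600 patients, recruited by 40 GPs, must be included and then divided into 300 patients in each arm". Under Statistical methods: "The tests will be two-sided, with a type I error set at" 0.05.

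The section Feasibility reports the pilot. Six of 13 intervention GPs recruited: "The GPs in the IG included 26 of their patients in the study". Thirteen of 24 control GPs recruited: "The GPs in the CG included 61 of their patients". The pilot's duration is not given. Under Recruitment, the main trial has 12 months of enrolment, with one call and two e-mails a month to each GP.

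**The concern.** Two things do not fit together. First, the abstract attaches 90% power to 600 patients at ICC 0.2, while the sample size section gives 800 for that same ICC. Second, the cluster size enters twice, once in the total (40 × 15) and once in the design effect, so the power depends heavily on it. The document's only observed yield is about a third of 15. The sample size section cites the pilot when it discusses the control-group rate, but does not mention the pilot's yield per GP.

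At stake is whether a reader, or the Steering Committee judging progress, can rely on the 90%. If the effect is as planned but power is nearer 80% or lower, a null result would carry less weight than the protocol suggests.

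**Working it through.** **Inputs.** Rates 5% and 20%, two-sided alpha 0.05 (normal quantile 1.960), target power 90% (quantile 1.282), 40 GPs, *m* = 15, ICC 0.05 to 0.20, losses of 10% (GPs) and 20% (patients), pilot counts 26 from 6 GPs and 61 from 13 GPs. All are from the protocol.

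**1. The plan's base figure.** With pooled rate 0.125,

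n per arm = [1.960 × √(2 × 0.125 × 0.875) + 1.282 × √(0.05 × 0.95 + 0.20 × 0.80)]² / 0.15² = (0.9167 + 0.5838)² / 0.0225 = 100.1, rounded up to 101.

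This reproduces 101, but per arm (202 in total), not in total as written. A total of 101 would give about 63% power.

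**2. The plan's clustered totals.** Design effect DE = 1 + (*m* − 1) × ICC, with *m* = 15:

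| ICC | DE | 202 × DE | Stated |
|---|---|---|---|
| 0.05 | 1.70 | 343 | 360 |
| 0.20 | 3.80 | 768 | 800 |
| 0.25 | 4.50 | 909 | about 960 |

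The stated totals are close to these and confirm that the base is about 202. The 600 does not correspond to ICC 0.20. It gives 90% only if DE = 600/202 = 2.97, that is, ICC = (2.97 − 1)/14 = 0.14.

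**3. Power of 600 patients.** Effective n per arm = N / (2 × DE), and

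power = Φ{[0.15 × √n − 0.9167] / √(0.05 × 0.95 + 0.20 × 0.80)} = Φ{[0.15 × √n − 0.9167] / 0.4555}.

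- ICC 0.20: n = 600/(2 × 3.80) = 78.9; power = Φ(0.913) = 82%.
- ICC 0.05: n = 600/(2 × 1.70) = 176.5; power = Φ(2.362) = 99%.

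If the stated losses both apply to the primary outcome, 36 GPs × 12 patients = 432:

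- ICC 0.20: DE = 1 + 11 × 0.20 = 3.20; n = 67.5; power 76%.
- ICC 0.05: DE = 1.55; n = 139.4; power 97%.

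**4. Sensitivity to *m*.** Pilot yield per recruiting GP: 26/6 = 4.33, 61/13 = 4.69, overall 87/19 = 4.58. Forty recruiting GPs at that yield give 40 × 4.58 = 183 patients.

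| ICC | DE at *m* = 4.58 | Effective n per arm | Power | Power at *m* = 15 | Difference (points) |
|---|---|---|---|---|---|
| 0.20 | 1.716 | 53.4 | 65% | 82% | 17 |
| 0.05 | 1.179 | 77.7 | 81% | 99% | 18 |

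The smaller clusters lower the design effect, but this recovers only part of what the smaller total loses. A *t* test on 38 degrees of freedom gives nearly the same results (65.0% and 80.7% at *m* = 4.58; 81.4% and 98.9% at *m* = 15).

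**The case against.** A reader might infer that the pilot shows the trial will recruit only about 183 patients and have 65% power instead of 90%. The documents do not support that, for three reasons.

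- The 4.6 is a count with no time denominator. At a constant pace, 15 per GP in 12 months would follow from a pilot lasting 12 × 4.58/15 = 3.7 months or less. The article does not say how long the pilot ran, and a condensed article may leave that to the full protocol. The main trial also has monthly reminders and a leading investigator in each region.
- The 65% holds only at ICC 0.20, the top of the range in the sample size section; at 0.05 it is 81%.
- Of the 25 points between 90% and 65%, 8 have nothing to do with recruitment, because the full 600 patients reach only 82% at ICC 0.20.

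It can also be said that 40 × 15 = 600 is correct arithmetic, that 15 is an approximate mean and not a quota for every GP, and that 600 is a requirement, not a forecast. All of that stands. So does the point that taking the pilot's event rates as well (6.6% v 30.8%) would give about 91% (ICC 0.20) and 98% (ICC 0.05) at the pilot yield. However, the plan deliberately uses the more cautious 5% v 20%, and its power claim has to be judged on those rates.

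None of this rescues the 90% at ICC 0.20. There the target is missed even if every planned patient is recruited, and the sample size section's own 800 says so.

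**Conclusion.** The concern holds in this form. The unconditional 90% is not what the design delivers at the ICC fixed in the abstract: it is 82% before losses and about 76% after them. At ICC 0.05 it is 99%, and 600 patients give 90% only at an ICC of about 0.14. The claim also rests on a mean of 15 patients per GP that is about 3.3 times the only yield reported (15/4.58). At that yield, power is 65% to 81% over the plan's ICC range, so 90% is missed throughout the range.

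The 82% and 99% follow from the plan's own inputs, using a pooled-variance comparison of two proportions and equal cluster sizes. The 76% assumes that both loss rates affect the primary outcome. The 65% and 81% further assume that the pilot yield carries over and that all 40 GPs recruit, with no losses. They are a sensitivity case, not a prediction; the plausible range of *m* runs from 4.6 to 15.

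**What to change.** In the abstract and in Sample size estimation, replace the single 90% with the power of 40 GPs × 15 patients by ICC: 99% at 0.05 and 82% at 0.20, before losses. Beside it, show the power at the pilot yield of 4.6 per recruiting GP, 81% and 65%, labelled as a sensitivity case, and state that 90% is not reached there.

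The cost is a recalculation and a few lines of text. No patients or GPs are added. The stated power becomes less favourable.

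### The sample size inflation factor uses only the mean number of patients per GP, so unequal recruitment leaves the power of 600 patients modestly overstated at the upper end of the ICC range

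*Protocol article*

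**What the plan says.** The Sample size estimation section of the protocol article starts from 101 patients for individual randomisation and multiplies by 1 + (m − 1) × ICC, where m is "the (mean) number of patients included by each GP". The plan "includes a recruitment of around 15 patients per GP". For m = 15, "sample size estimation was 360 for ICC equals 0.05 and 800 for ICC at 0.20, and around 960 for ICC at 0.25". The section then settles on 600 patients from 40 GPs, 300 per arm. The Abstract attaches 90% power and an ICC of 0.2 to those 600.

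Three other sections bear on the point:
- Feasibility: 6 of 13 intervention GPs and 13 of 24 control GPs in the pilot included any patient. They included 26 and 61 patients respectively.
- Allocation: the surgery is the unit of randomisation, and GPs who share a surgery go to the same arm.
- Statistical methods: a generalised linear mixed model is the primary analysis. Cluster-level comparisons with ordinary tests are also planned, and no weighting is mentioned.

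**The concern.** The simple inflation factor is exact only if every cluster contributes the same number of patients. When sizes vary around the same mean, the large clusters add less information than the small ones lose, so the trial is less precise than the factor implies. This holds even if the mean of 15 is reached and all 40 GPs recruit.

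The article's own wording allows for variation (a mean, of around 15), but the calculation has no term for it. The pilot gives no support for equal sizes, and clusters defined by surgery will also differ in how many GPs they contain. The omission makes a required sample size too small and a stated power too high. What is at stake is whether the power claimed for 600 patients can be relied on, chiefly where the ICC is high.

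**Working it through.** **Inputs from the article.** Sample size estimation gives 5% versus 20% ("We estimated the incidence in the CG at around 5" per cent for the control arm), a two-sided α of 0.05, 90% power, m = 15, ICC 0.05 to 0.20 with 0.25 also shown, and 300 patients per arm.

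**Assumed input.** The CV of cluster size is not in the documents. Values of 0.5, 0.65 and 0.8 are used.

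**1. Base size.** The pooled two-proportion formula is

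n = [1.960 × √(2 × 0.125 × 0.875) + 1.2816 × √(0.05 × 0.95 + 0.20 × 0.80)]² / 0.15² = (0.9167 + 0.5838)² / 0.0225 ≈ 100.1, rounded up to 101.

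This is 101 per arm, or 202 in all, although the article labels 101 as a total. The stated clustered sizes are consistent only with the per-arm reading.

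**2. The article's clustered sizes, with equal clusters.**

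| ICC | 1 + 14 × ICC | 202 × factor | Stated | Excess |
|---|---|---|---|---|
| 0.05 | 1.70 | 343 | 360 | 4.8% |
| 0.20 | 3.80 | 768 | 800 | 4.2% |
| 0.25 | 4.50 | 909 | 960 | 5.6% |

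The stated sizes are not reproduced exactly. They lie 4 to 6% above the plain formula, which leaves some slack.

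**3. Factors for unequal clusters.**
- Mixed model (efficient weighting, approximate): [1 + (m − 1)ICC] / [1 − CV² × L(1 − L)], with L = m × ICC / [1 + (m − 1)ICC]. At ICC 0.20, L = 3/3.8 = 0.789 and L(1 − L) = 0.166. The denominators are 0.958, 0.930 and 0.894, so the factors are 3.96, 4.09 and 4.25.
- Unweighted (pessimistic bound): 1 + [(1 + CV²)m − 1] × ICC. At ICC 0.20 this gives 4.55, 5.07 and 5.72.

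**4. Size needed for 90% power (202 × factor).**

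| CV | ICC 0.05, mixed model (stated 360) | ICC 0.20, mixed model (stated 800) | ICC 0.25, mixed model (stated 960) | ICC 0.20, unweighted |
|---|---|---|---|---|
| 0.5 | 366 | 801 | 942 | 919 |
| 0.65 | 383 | 826 | 966 | 1,024 |
| 0.8 | 408 | 859 | 998 | 1,155 |

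Under the mixed-model factor, the stated sizes keep 90% power up to a CV of about 0.43, 0.49 and 0.62 at ICC 0.05, 0.20 and 0.25. Under the unweighted bound they do so up to about 0.33, 0.23 and 0.26.

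**5. Power of 600.** Each arm has an effective size of 300/factor, and power = Φ[(0.15 × √(300/factor) − 0.9167) / 0.4555]. With equal clusters at ICC 0.20, 300/3.8 = 78.9, so power = Φ(0.913) = 82%.

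| CV | ICC 0.20, mixed model | ICC 0.20, unweighted | ICC 0.05, mixed model | ICC 0.05, unweighted |
|---|---|---|---|---|
| 0 | 82% | 82% | 99% | 99% |
| 0.5 | 80% | 75% | 99% | 98% |
| 0.65 | 79% | 70% | 98% | 98% |
| 0.8 | 77% | 65% | 98% | 97% |

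These figures take all 600 patients as analysed, before the losses listed in the Abstract. With equal clusters, 600 patients give 90% power only up to an ICC of (300/101 − 1)/14 = 0.14.

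**The case against.** The strongest reply is that the formula is standard and correct for the planned mean, and that a condensed article may leave a refinement for unequal clusters to the full protocol. The stated sizes also exceed the plain formula by 4 to 6%, and the primary mixed model loses far less than the unweighted bound suggests. Much of this stands. It limits the size of the problem but does not remove it: the article prints the factor and attaches a definite 90% to 600 patients, and both can be checked as stated.

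Some stronger readings are tempting but not supported:
- A reader might infer that every size in the section is too small. At ICC 0.25 and CV 0.5 the mixed model needs 942, against 960 stated. At ICC 0.20 and CV 0.5 it needs 801 against 800. At ICC 0.05 the chosen 600 is ample.
- A reader might take power of 65 to 75% as the expected result. Those figures belong to an unweighted analysis, which is not the primary one.
- A reader might blame unequal recruitment for the whole gap from 90%. At ICC 0.20 power is already 82% with equal clusters, because 600 patients were chosen where the article gives 800.
- A reader might take a CV from the pilot. With 18 of 37 GPs including nobody, the CV across all 37 is at least √(18/19) = 0.97. That value mixes inactive GPs with variation among active ones. The article reports only totals for the active GPs (26/6 = 4.3 and 61/13 = 4.7 patients each), so their CV is unknown.

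**Conclusion.** The point holds, with a modest effect confined to the upper part of the ICC range. The inflation factor allows nothing for unequal clusters, while the pilot and randomisation by surgery make equal clusters implausible.

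For assumed CVs of 0.5 to 0.8 at ICC 0.20, the size needed under the planned mixed model is 0.1 to 7% above the stated 800. The power of 600 is about 2 to 5 percentage points below its equal-cluster value of 82%. An unweighted GP-level test could lose about 7 to 17 points. At ICC 0.05 power stays above 95% under either factor.

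The larger shortfall, from 90% to 82%, is the separate conflict between 600 and 800 patients and would remain if every GP included exactly 15. The sizes given here rest on the assumed CVs and on an approximate efficiency formula for the mixed model.

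**What to change.** In Sample size estimation:
- Replace the factor by [1 + (m − 1)ICC] / [1 − CV² × L(1 − L)], with L = m × ICC / [1 + (m − 1)ICC]. This matches the mixed model named as the primary analysis.
- State the assumed CV and show a range. If the sponsor holds per-GP counts from the pilot they can inform it, but at 4 to 5 patients per recruiting GP they would not settle it.
- Restate the power of 600 patients at ICC 0.20 (about 77 to 80% for CVs of 0.8 to 0.5, before losses), align the Abstract with it, and reconcile 600 with the 800 given for that ICC.

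In Statistical methods, state that any GP-level comparison is weighted by cluster size.

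The cost is rewording and a less favourable stated power. No additional patients and no change to recruitment are asked for.

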## Abstract

**Background:**

Premature ejaculation (PE) is the most common sexual dysfunction among men. According to patients, the general practitioner (GP) is the appropriate professional with whom to discuss this issue. However, few patients receive the medical help needed because GPs find it difficult to talk to their patients about sex. A previous qualitative study provided six strategies described by GPs who had tackled the topic during consultation. A pilot study showed that using one of these strategies after a training course led to an increase in the rate of consultations where the topic was raised: an increase from 6.6 to 30.8%. The aim of this study is to compare whether training in communication skills with these six strategies is more effective than usual care on the incidence of patients bringing up the topic of PE with their GP.

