## Methods

### Outcome

The primary outcome is the incidence of patients bringing up the topic of PE with their GP.. This was undertaken in the group where the GPs received training in communication skills directed towards this pathology, compared with the patients who received the usual care procedures.

The secondary outcome relates to the variation in the quality of life of patients after they have addressed the topic of PE as measured by the SF-12 questionnaire.

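### The pilot rates behind the sample size carry two incompatible labels, and the 5% control rate rests on a latency prevalence that measures neither event

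*Protocol article*

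**What the plan says.** The Outcome section defines the endpoint: "The primary outcome is the incidence of patients bringing up the topic of PE with their GP". The Sample size estimation section sizes the trial for a difference "in terms of the incidence of new cases of patients bringing up the topic of PE with their GP".

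Three places report the same pilot rates:

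- Feasibility says the pilot was meant to estimate feasibility "as well as the incidence of diagnosed PE with, and without, the use of strategies". It gives 8 of 26 intervention patients (30.8%) as identified as suffering from PE. Of the 61 control patients it says: "Among them, four were suffering from PE: 6.6" per cent.
- The Abstract (Background) says that using a strategy "led to an increase in the rate of consultations where the topic was raised: an increase from 6.6 to 30.8" per cent.
- Sample size estimation says: "In our feasibility study, the incidence of patients who brought up PE with their GP in the CG was 6.6" per cent.

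The last section then cites the sexual-medicine guideline, "5% of the population have an ejaculation latency of less than 2 minutes", and concludes: "We estimated the incidence in the CG at around 5" per cent. The design contrast is 5% against 20%, with two-sided alpha 0.05 and 90% power. The Abstract (Methods) lists an ICC of 0.2 and a Hawthorne effect of 15% among the inputs to the 600 patients.

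**The concern.** Raising PE in a consultation and being found to have PE are different events. A man may raise the topic and not have the condition, or have it and never mention it. One count cannot be assumed to estimate both, yet the article attaches both descriptions to it.

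The step from 6.6% to 5% is a second problem. The share of the general population with a short latency is not a rate of raising a topic. Nor is it a rate of PE identified by questionnaire or by the GP among men who consult for a sexual, urogenital or psychological reason. The article's own Background warns against this substitution: it gives a prevalence of 30% by self-report and 3% when time is considered alone. The direction is also awkward, because the Discussion expects control GPs' awareness of the topic to raise the rate.

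At stake is an input on which the stated power rests.

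**Working it through.** **Inputs.** Pilot counts 8/26 and 4/61 (Feasibility). Design rates 5% and 20%, power 90%, ICC 0.05 to 0.20, about 15 patients per GP, 300 patients per arm (Sample size estimation). Two-sided alpha 0.05 (Statistical methods).

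**Pilot percentages.** 4/61 = 6.6% and 8/26 = 30.8%. The figures in all three sections therefore come from these counts. The exact 95% interval for 4/61, ignoring clustering, is 1.8% to 15.9%.

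**The plan's own figure.** The pooled two-proportion formula, with p̄ the mean of the two rates, is

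n per arm = [1.960·√(2p̄(1−p̄)) + 1.2816·√(p1(1−p1) + p2(1−p2))]² / (p1−p2)²

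At 5% v 20%: (1.960 × 0.4677 + 1.2816 × 0.4555)² / 0.15² = 100.06, rounded up to 101. This recovers the printed 101, but as a number per arm, not in total as printed (a separate matter). It confirms that 5% is the operative input.

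**At the pilot control rate, with 20% kept.** (1.960 × 0.4802 + 1.2816 × 0.4708)² / 0.134² = 132.9, rounded up to 133 per arm, which is 32% more.

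**Power of 600 patients before losses.** The design effect is 1 + 14 × ICC, so 3.8 at ICC 0.20 and 1.7 at ICC 0.05. The effective number per arm is 300/3.8 = 78.9 or 300/1.7 = 176.5. With n the effective number per arm,

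power = Φ{[|p1−p2|·√n − 1.960·√(2p̄(1−p̄))] / √(p1(1−p1) + p2(1−p2))}

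| Control v intervention | n per arm before clustering | Power, ICC 0.20 | Power, ICC 0.05 |
|---|---|---|---|
| 5% v 20% (as designed) | 101 | 82% | 99% |
| 6.6% v 20% | 133 | 70% | 96% |
| 6.6% v 21.6% (15-point difference kept) | 112 | 78% | 98% |
| 6.6% v 30.8% (both pilot rates) | 53 | 98% | over 99% |

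**Pilot test statistics.** Feasibility prints OR 6.6768, 95% CI 1.55 to 34.40, p = 0.004. From 8/26 v 4/61, the sample odds ratio is (8 × 57)/(18 × 4) = 6.33. The conditional estimate is 6.17, with exact CI 1.45 to 31.4 and Fisher p = 0.0053. The printed values do not belong to the printed counts.

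**The case against.** Four points can be made for the plan.

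First, if the pilot GPs could identify PE only when it had been discussed, the two counts may largely coincide and the relabelling is loose wording. This is possible. But Feasibility does not say how the four control patients were identified, so it cannot be confirmed. For the same reason, the tempting reading that 6.6% is a lower bound for topic raising is not supported. If a questionnaire was used, some of the four may never have raised the topic, and 6.6% would be too high.

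Second, Outcomes and measurements and Statistical methods describe the analysed endpoint as patients suffering from PE. On that version the Feasibility count is the matching event. This stands, and it means the endpoint itself is unsettled. It does not rescue the 5%, because a latency prevalence matches neither version.

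Third, a reader might infer that every step pushes the control rate down and flatters the power. Relabelling leaves the rate at 6.6%; only the move to 5% lowers it, and 5% lies well inside the pilot interval. The plan also cut the intervention rate from 30.8% to 20%, so the assumed difference shrank from 24.2 to 15 points. This stands.

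Fourth, the fall to 70% depends on holding 20% fixed. Sample size estimation frames the target as an absolute difference, and keeping 15 points gives 78%. This also stands.

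**Conclusion.** The point holds as one of labelling and justification. The same pilot counts are given two meanings, the documents do not settle which is right, and the 5% comes from a quantity that is not the outcome under either meaning.

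The size depends on what is held fixed. Against the designed 82% at ICC 0.20, using 6.6% gives 70% with 20% kept or 78% with the 15-point difference kept; the pilot's own contrast gives 98%. At ICC 0.05 the figure is 96% or more in every case. These results assume equal clusters of 15, no losses, and a control rate of 6.6% that is itself imprecise.

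A reader might infer that 600 patients are too few because of the control rate. The documents do not support that. The gap between the stated 90% and 82% at ICC 0.20 exists already at 5% v 20%, and reflects choosing 600 when the plan's own figure for that ICC is 800.

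The mismatch in the pilot odds ratio, interval and p-value is certain, but it is a separate reporting error that does not enter the sample size. A table of 8/24 v 4/59 comes very close to the printed values, so a reader might infer that two patients per arm were left out. The documents do not say so, and the cause is unknown.

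**What to change.** - Recount from the existing pilot records, in each arm and with its denominator, the event that matches the primary outcome. Correct the Abstract, Feasibility and Sample size estimation so that each rate names the event counted. Reconcile this with the endpoint wording in Outcomes and measurements and in Statistical methods.
- Remove the latency prevalence as a justification for the control rate.
- Restate the power of the 600-patient design at the recounted control rate, or at the pilot's 6.6% if no recount is possible. Say whether 20% or the 15-point difference is held.
- State how the 15% Hawthorne allowance enters the calculation, so that it is not applied once as an inflation and again to the control rate.
- Separately, correct the pilot odds ratio, interval and p-value, or the counts, so that they agree.

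The cost is a check of 87 records (26 + 61), a few corrected sentences and a restated power figure. Enrolment does not change.

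### The 101 patients for 5% against 20% are per arm, not in total, and 600 patients do not give 90% power at ICC 0.2 with the stated losses

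*Protocol article*

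**What the plan says.** The Sample size estimation section sets the control rate ("We estimated the incidence in the CG at around 5" per cent) and states that under individual randomisation "101 patients in total is necessary to highlight an absolute difference between 5 and 20" per cent. The error rates follow at once: alpha "equals 0.05 and has a statistical power of 90" per cent. The Statistical methods section confirms the sidedness: "The tests will be two-sided, with a type I error set at" 0.05.

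The section multiplies by the usual factor 1 + (m − 1) × ICC and plans for an ICC from 0.05 to 0.20. With 15 patients per GP it gives the cluster-adjusted size as "360 for ICC equals 0.05 and 800 for ICC at 0.20, and around 960 for ICC at 0.25". It then ends on 600 patients from 40 GPs, 300 per arm.

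The abstract repeats the base figure without saying whether it is a total ("The number of patients necessary to highlight a significant difference between the two groups from 5 to 20% is 101") and goes on: "Therefore, a total of 600 patients is expected, 300 in each arm (40 GPs, 15 patients per GP". The same parenthesis lists alpha 5%, power 90%, ICC 0.2, a Hawthorne effect of 15%, and "lost-to-follow-up rates for GPs = 10% and for patients = 20" per cent.

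**The concern.** Two statements look wrong on their face. First, 101 is too few in total for these rates at 90% power. Second, the section asks for 800 at ICC 0.20 before any allowance for loss, while the abstract offers 600 at that same ICC with losses and a Hawthorne effect on top. Both cannot describe a 90%-power design.

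The stated power governs how a null result is read. If the true power at the stated ICC is nearer 76% to 82%, the type II risk is 18% to 24%, not 10%, and a negative trial would be given more weight than it deserves.

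**Working it through.** **Inputs, all from the article.** Rates 5% and 20%; two-sided alpha 0.05 (z = 1.960); power 90% (z = 1.2816); m = 15; ICC 0.05 to 0.20; 40 GPs; 600 patients; losses of 10% of GPs and 20% of patients.

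**1. The base number.** Pooled two-proportion formula, mean rate 0.125:

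n per arm = [1.960 × √(2 × 0.125 × 0.875) + 1.2816 × √(0.05 × 0.95 + 0.20 × 0.80)]² / 0.15² = (0.9167 + 0.5838)² / 0.0225 = 100.06, so 101.

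This reproduces the article's 101 exactly, but per arm. The total is 202. With 101 per arm the power is 90.3%; with 101 in total (50.5 per arm) it is 63%. Other standard two-sided formulas give totals of 194 (unpooled), 186 (arcsine) and 228 (continuity-corrected). One-sided versions at 90% power need at least 152. None gives 101 in total.

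**2. The article's cluster-adjusted figures.** Divide each by its design effect:

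- 360 / 1.7 = 212
- 800 / 3.8 = 211
- 960 / 4.5 = 213

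These rest on a base of about 211 in total, close to 202 and far from 101. From 202 at ICC 0.20 the size is 202 × 3.8 = 767.6, so 768. Either way, the need at ICC 0.20 exceeds 600 before any loss.

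**3. Power of 600 by the design-effect method.** Effective n per arm = N / (2 × DE); power = Φ[(0.15 × √n − 0.9167) / 0.4555].

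- No loss, ICC 0.20: 600 / (2 × 3.8) = 78.9 per arm, power 82%.
- GP loss only (36 GPs × 15 = 540): 71.1 per arm, power 78%.
- Both losses (36 GPs × 12 = 432, DE = 1 + 11 × 0.20 = 3.2): 67.5 per arm, power 76%. Keeping DE at 3.8 would give 68%.

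| ICC | DE at m = 15 | Power, 600, no loss | DE at m = 12 | Power, 432, both losses |
|---|---|---|---|---|
| 0.05 | 1.70 | 99% | 1.55 | 97% |
| 0.10 | 2.40 | 95% | 2.10 | 91% |
| 0.15 | 3.10 | 89% | 2.65 | 83% |
| 0.20 | 3.80 | 82% | 3.20 | 76% |

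**4. Largest ICC at which 90% holds.** No loss: (600/202 − 1)/14 = 0.14. Both losses: (432/202 − 1)/11 = 0.10.

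**5. The planned analysis.** The article names a generalised linear mixed model as primary analysis. In a simulation of that model (beta-binomial data, ICC 0.20, 2,000 runs), power was about 90% for 40 GPs × 15 and about 85% for 36 GPs × 12.

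**The case against.** The best defence is that the design-effect formula is only an approximation and that the planned mixed model reaches about 90% for 40 × 15 at ICC 0.2. This stands in part. With no loss, the mixed model supports the stated power. A second simulation (800 runs, likelihood-ratio test) gave 92% with no loss, 89.5% with GP loss only and 85% with both losses. Its type I error was about 6.6% to 7%, so these figures are somewhat flattering; a cluster-level t test gave 85%, 80% and 77%. The abstract claims 90% with both losses listed, and there no method checked reaches it.

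It can also be said that the 20% patient loss may not touch the primary outcome. The Outcome section defines it as raising the topic with the GP, which happens at the consultation, whereas the 4-week return carries the SF-12 and PEDT. That is fair, although the Outcomes and measurements and Statistical methods sections tie incidence to diagnostic categories that depend on the returned PEDT. Without patient loss, design-effect power is 78% to 82%, and the mixed model is close to 90%.

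Thirdly, the article plans over a range of ICC and calls the value hard to fix. At 0.05 to 0.10, 600 gives 97% to 91% after both losses. That stands too: the shortfall lies at the upper end of the range, but that is the end the abstract names.

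A reader might infer that 600 was obtained by carrying 101 forward as a total, since 101 × 3.8 × 1.15 × 1.10 × 1.20 = 583. The documents do not establish this. The article's own 360 at ICC 0.05 fits about as well: 360 / (0.85 × 0.90 × 0.80) = 588, or 360 × 1.15 / 0.72 = 575. The 360, 800 and 960 were plainly not built on 101. The derivation of 600 is not shown, and the shortfall does not depend on it.

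**Conclusion.** The point holds on two counts. The label on 101 is wrong: it is the number per arm, and the total is 202. The abstract's 90% power at ICC 0.2 with 600 patients conflicts with the 800 in the Sample size estimation section. By that section's own method, the power at ICC 0.20 is about 82% with no loss, 78% with GP loss only and 76% with both; 90% holds only up to an ICC of about 0.14 without loss or 0.10 with both losses. The planned mixed model narrows the gap (about 90% and 85%) but does not close it under both stated losses.

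The after-loss figures assume equal cluster sizes, 36 GPs with 12 analysed patients each, and that patient loss affects the primary outcome. No Hawthorne allowance is included. A reader might take the 15% as a higher control rate or a smaller difference and conclude that power is lower still. The article does not say what the 15% acts on, so no figure for it can be treated as a result. Nor do the documents support saying that 600 is inadequate throughout the planned ICC range.

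**What to change.** - In Sample size estimation, change the base figure to 101 per arm (202 in total), and add the same label in the abstract.
- Reconcile 800 with 600 at ICC 0.20 by stating how 600 was reached and which ICC and allowances it covers.
- Keep 600. Where the abstract and the end of Sample size estimation tie it to 90% power at ICC 0.2, give instead the power that 600 delivers over ICC 0.05 to 0.20, before and after losses, naming the method. By design effect this is 99% down to 82% before losses and 97% down to 76% after both. A simulation of the mixed model may be reported alongside, with its type I error.
- State what the 15% Hawthorne effect acts on: the control rate, the difference, or the number recruited.

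The cost is a rewording of one section and the abstract, and a less favourable stated power at the upper ICC. No patients, GPs or procedures are added.
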